### Study design and setting

The sheMATTERS trial is a multicenter, open-label, RCT conducted at four publicly funded, university-affiliated teaching hospitals in Canada (three located in Montreal, Quebec and one in Kingston, Ontario) with ~ 12,000 annual deliveries combined. The trial is registered on ClinicalTrials.gov (identifier # NCT04580927; see Additional file 4: Appendix 1 for Trial Registration Data Set). The coordinating center, the Research Institute of the McGill University Health Center (RI-MUHC), is responsible for overall data management, monitoring, and communication among all sites, and general oversight of the research project.

### Participants and recruitment

We are recruiting eligible postpartum (*N* = 278) breastfeeding parents with HDP into the RCT to assess the effect of the BSEI on BP and breastfeeding outcomes. In addition, we are recruiting (*N* = 45) non-breastfeeding parents with HDP into a non-randomized observational arm of the study, serving as a comparison group. Inclusion criteria include: having a diagnosis of HDP, as per the 2018 International Society of Hypertension in Pregnancy (ISSHP) classifications [80], age ≥ 18 years, singleton live birth delivered at ≥34 weeks gestation, speaks and understands English or French, has cellular phone and internet access, has a valid health insurance card at time of recruitment, and (for those in the randomized arm), intends to breastfeed and initiates breastfeeding or milk expression prior to hospital discharge. Exclusion criteria include: maternal intensive care unit admission lasting > 24 hours, severe or uncontrolled psychiatric illness that would preclude active engagement in the study, active COVID-19 infection at time of postpartum hospitalization, or previous participation in the trial’s pilot study. In addition, breastfeeding individuals are excluded from the randomized arm if they or their infant have any absolute contraindication to breastfeeding (e.g., HTLV-1 infection; galactosemia) or conditions that may interfere with successful initiation of breastfeeding (e.g., history of breast reduction surgery; infant with cleft palate).

Potential participants are identified and recruited from the hospitals’ antenatal, intrapartum or postpartum units by trained research assistants. Participants may also be referred antenatally to the research team by their obstetrical care provider or self-refer in response to recruitment posters and flyers distributed in the participating centers. The research staff meet with interested participants in person or via telephone to assess eligibility, and obtain informed verbal and written consent (see Additional file 5: Appendix 2). All eligible persons, including those who decline participation in the RCT or observational arms of the study, are additionally invited to participate in an independent long-term passive follow-up study via electronic health record data linkage.

All participants have the ability to withdraw at any time before study completion. Participation may also be stopped by the research team if a second pregnancy occurs during the 12-months study, or if it is in the best interest of participants (i.e., new medication, participant’s mental health condition). Data collected until then is kept guaranteeing the integrity of the study conduct but will not be used for analysis.

### Randomization procedures

After giving birth, all eligible and consenting postpartum individuals who are planning to breastfeed are enrolled in the RCT and randomly allocated by the research assistant to either the control group (usual in-hospital and community postpartum care only) or intervention group (usual in-hospital and community postpartum care plus the BSEI with an assigned lactation specialist). A usual care group as a primary comparison arm is best suited to assess the effectiveness of a behavioral intervention. A central random allocation sequence is computer-generated (via REDCap) stratified by study site, with an allocation ratio of 1:1 using random block sizes of 2, 4 and 6. Allocation is concealed to all research team members until randomization. The research assistant informs the participants of their group allocation immediately after they’ve completed their baseline measures. Although the RCT participants cannot be blinded, data oversight and analysis will be performed by research personnel blinded to group allocation.

### Usual postpartum care and non-breastfeeding comparison groups

All study participants, regardless of intervention status, receive usual in-hospital and community postpartum care. In Quebec and Ontario, length of postpartum hospitalization for those with HDP is on average 24 hours longer than the standard stay of 24–36 hours following uncomplicated vaginal birth, and 72 hours following cesarean section. In Quebec, community-based public health nurses routinely contact all postpartum parents via telephone within 72 hours of hospital discharge. In-hospital and community-based perinatal nurses have at least basic training in breastfeeding assessment and support. Other breastfeeding resources that may be available to all participants include access to hospital-based lactation consultants, government-issued booklets on infant care, resource lists for community-based breastfeeding support and on-line breastfeeding support websites. In Ontario, education sessions are available for new parents to help with newborn care and feeding. In addition, a public health nurse may visit and offer breastfeeding support, and teach parents how to care for themselves and their baby. Home and Community Support can also provide assistance and resources. As part of usual clinical care post-HDP, all study participants are also scheduled for an in-person appointment at the Maternal Cardiovascular Health Clinic (Montreal), or the Maternal Health Clinic (Kingston) at 6- and 12-months postpartum.

As a token of appreciation for their participation in the study, participants receive a gift bag valued at $20.00 CDN containing samples of newborn products from collaborating suppliers immediately after informed consent has been obtained. In addition, at the end of the study, participants receive a gift card valued at $20.00 CDN. In recognition of their time and effort, participants are compensated for parking or transportation expenses in the amount of $10.00 CDN per in-person study visit, for a total of two visits. Funding for this expense is covered by [name] Career Professorship in Women’s Heart Health from the Heart and Stroke Foundation of Canada (Fund #252076).

### Intervention group

In addition to usual care and anything sought out in the community, participants allocated to the BSEI receive individualized breastfeeding support from a trained research lactation consultant. The BSEI consists of two in-hospital, one-on-one BSE-enhancing sessions prior to postpartum discharge, weekly proactive telephone follow-up calls from the lactation consultant for the first 6 weeks post-hospital discharge, and a telephone BSE-enhancing “booster” session at 3 months. In addition, the lactation consultant is available via phone or text for participant-initiated retroactive breastfeeding support for up to 6 months postpartum (the recommended duration of exclusive breastfeeding) (Fig. 3).

The BSE-enhancing sessions were adapted from a BSEI developed by co-investigator [name] that has been pilot-tested [81] and recently trialed with almost 1000 first-time parents in Canada (ISRCN.com, #85493925). The sessions last on average 60 minutes and follow a standardized format of 1) assessment of the participant’s breastfeeding goals, general physiologic state (e.g., pain, fatigue), and level of BSE using the Breastfeeding Self-Efficacy Short Form (BSES-SF) [71]_,_ 2) observation of the participant’s breastfeeding or milk expression attempts (when possible), and 3) implementation of tailored BSE-enhancing breastfeeding management strategies based on the four sources of self-efficacy information [69]. For example, if the participant indicates low confidence for the BSES-SF item: *“I can always determine that my baby is getting enough milk”,* individualized interventions may include pointing out observable cues of effective infant latch and milk transfer at the breast (performance accomplishments), praising successful breastfeeding attempts (verbal persuasion), and using visual aids to describe newborn milk-volume requirements during the first days of life (vicarious learning). For participants with infants admitted to the neonatal intensive care unit (NICU), the BSE assessment is conducted using the BSE scale adapted for parents with ill or preterm infants [72]. The first in-hospital BSE-enhancing session occurs as soon as possible following randomization to the BSEI. Immediately upon allocation of a participant to the BSEI, the study’s lactation consultant is notified and contacts the participant via telephone to arrange a time for the first BSE-enhancing session (ideally to coincide with an infant feeding). The session may be conducted in the participant’s postpartum hospital room or at the infant’s bedside in the NICU, as needed. A second BSE-enhancing session is scheduled prior to the participant’s hospital discharge if time permits, to continue the breastfeeding management strategies and reinforce improved performances. If the lactation consultant is restricted from visiting the hospital units due to COVID-19 infection control procedures, the in-hospital BSE-enhancing sessions will be conducted remotely by telephone and/or videoconferencing using the research team’s confidential ZOOM™ license. The 3-month telephone BSE-enhancing “booster” session is conducted by telephone, with the option of videoconferencing via ZOOM™ if observation of an infant feeding session is needed for the breastfeeding assessment. The goal of the 3-month session is to provide BSE-enhancing strategies for any new or ongoing breastfeeding issues and to boost participants' confidence and commitment to sustain exclusive breastfeeding up to 6 months.

As the first 6 weeks postpartum has been identified as a critical time-period for the establishment of successful lactation [82], the first follow-up telephone call from the lactation consultant is scheduled for 7 days post-discharge, and then once weekly thereafter for 6 weeks. Up to five attempts to contact the participant via either phone or text is made for each follow-up call. These proactive calls last on average 30 minutes and follow a standardized format of 1) assessment of the participant’s breastfeeding status and physiological state, 2) review of lactation progress since last contact, and 3) implementation of BSE-enhancing breastfeeding management strategies tailored to the participant’s ongoing issues or concerns. For the retroactive telephone breastfeeding support, BSEI participants are provided with the lactation consultant’s cell phone number and encouraged to call or text for any additional breastfeeding related-questions or support needed, up to 6 months postpartum.

### Study outcomes

Our primary study endpoint is average systolic and/or diastolic BP, in mmHg, measured by standard recommended technique using validated automated office blood pressure devices. In the case of home blood pressure, an average of four daily measurements over a one-week period is used, after discarding the first day of measurement. Blood pressure data is collected at baseline, 6 weeks, 3 months, 6 months, and 12 months postpartum with the primary outcome at 12 months with repeat blood pressure and other cardiometabolic markers, as well as novel biomarkers. The purpose of the latter measurement is a secondary aim of sheMATTERS, which is enhanced cardiovascular phenotyping of those with HDP.

Our secondary study endpoint includes 1) elevated blood pressure (displayed automated mean blood pressure > 135 mmHg systolic and/or > 85 mmHg diastolic) or use of/increase in previous use of antihypertensive drug therapy, and 2) the presence of metabolic syndrome [83]. An additional secondary endpoint is systolic and/or diastolic blood pressure at 6months postpartum.

Breastfeeding outcomes include the duration of exclusive breastfeeding (in weeks), total breastfeeding duration (in weeks), the proportion of participants exclusively breastfeeding at 6 months, and the proportion of participants continuing any breastfeeding at 6 months and 12 months. Given high rates of in-hospital formula supplementation of breastfeeding infants born to persons with HDP [50], we have defined exclusive breastfeeding as the provision of nothing but breastmilk (either at the breast or via milk expression) after the first 7 days of life.

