**Fig. 3 Fig3:**
[figure not shown]
sheMATTERS Study Schemata. Schema of the sheMATTERS randomized behavioral trial design, additional comparison group, and long-term pragmatic cohort

The primary study objective is to assess whether the BSEI will result in lower systolic and/or diastolic BP, or a lower need for antihypertensive therapy at 12 months postpartum. Secondary study objectives are to 1) assess whether the BSEI will result in higher rates of exclusive and any breastfeeding at 6 months, as well as continued breastfeeding to 12 months; 2) assess whether the BSEI will decrease the rate of having metabolic syndrome at 12 months postpartum; 3) explore maternal blood pressure trajectories over time according to ‘dose’ of breastfeeding; 4) evaluate whether those who breastfeed for longer are more likely to engage in other cardiovascular protective behaviors, such as weight reduction, healthy eating, and higher levels of physical activity at 6 and 12 months postpartum; 5) explore the biological and psychosocial determinants of breastfeeding behavior to 12 months postpartum among those with HDP; and 6) collect bio-samples to measure key inflammatory and angiogenic factors from participants who recently had HDP to advance our understanding of the different phenotypes of these individuals and their associated cardio-metabolic risk in the short and long-term.

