### sheMATTERS trial hypotheses

The primary study hypotheses are that 1) individuals with HDP who receive the BSEI will have lower BP (approximately 5 mmHg systolic and/or 2 mmHg diastolic) compared to those who do not breastfeed, and 2) individuals with HDP who receive the BSEI will have a lower demand for antihypertensive treatment at 12 months postpartum compared with those who receive usual postpartum care. The secondary hypotheses are that:there will be a modest (10–20%) relative benefit in breastfeeding outcomes among participants with HDP who receive the BSEI compared to those who receive usual postpartum care;there will be a lower rate of metabolic syndrome in participants with HDP who receive the BSEI compared to those who receive usual postpartum care, and a greater difference when compared to those who do not breastfeed;rates of breastfeeding duration and exclusivity will be correlated with a greater tendency towards more cardioprotective behaviors over 12 months postpartum;infant neurodevelopment will be positively correlated with longer duration of any breastfeeding;severity of HDP, obesity, markers of inflammation, as well as education level and psychological symptoms at birth will be correlated with breastfeeding duration and exclusivity over 12 months postpartum.

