### Statistical analysis

Descriptive statistics will be used to characterize the study population. We will compare baseline characteristics in the experimental study arms to assess randomization effectiveness. We will assume two-sample tests such as chi-square tests, t-tests, and non-parametric tests as appropriate to assess between-group differences in various characteristics and outcome measurements. They include proportion on antihypertensive drug therapy, proportion of EBF at 6 months, total breastfeeding duration in weeks, total EBF in weeks, metabolic syndrome, as well as differences in physical activity and dietary patterns. Differences in the primary outcome between the intervention and control groups on study outcomes will be assessed using an intent-to-treat approach. To examine the effect of BSEI on systolic and/or diastolic BP at 12 months, we will use generalized linear regression (GLM) to model for continuous BP readings and the Generalized Estimating Equation (GEE) analyses using logistic regression (reduction of 5 mm in SBP from the baseline vs. no change). We will calculate beta estimates with 95% confidence intervals (CIs) after adjusting for any observed between group differences despite randomization. Given that we plan to recruit non-breastfeeding parents (*N* = 45), we will model breastfeeding first as a continuous exposure variable (number of weeks) with systolic BP as the outcome in a multivariable linear regression model. We will also evaluate the dose-response of breastfeeding categories (i.e., none, < 3 months, < 6 months, > 6 months) to determine systolic and diastolic BP trajectories. In a sensitivity analysis, we will use different combinations of systolic blood pressure and diastolic blood pressure, and delta change in BP from baseline will be assessed. Breastfeeding duration will be divided into quintiles/quartiles, and those will be correlated with a series of BP measures. We will also perform a survival analysis modeling time to cessation of exclusive breastfeeding in both study groups. The model will incorporate interval censoring and compare differences between groups controlling for variables of interest, such as baseline self-efficacy score, maternal education, income, and age. Kaplan-Meir curves and cox-regression will be used to address these aspects.

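### The article disagrees with itself on what is primary, and a primary endpoint of systolic and/or diastolic BP names no deciding variable

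*Protocol article*

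**What the plan says.** Four places in the protocol article bear on what is primary.

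- **Study outcomes, primary endpoint:** "Our primary study endpoint is average systolic and/or diastolic BP, in mmHg", taken at 12 months.
- **Study objectives, primary objective:** the trial is to assess "whether the BSEI will result in lower systolic and/or diastolic BP, or a lower need for antihypertensive therapy at 12 months postpartum".
- **sheMATTERS trial hypotheses:** primary hypothesis 1 expects a BP difference of "approximately 5 mmHg systolic and/or 2 mmHg diastolic". Primary hypothesis 2 is that participants given the intervention "will have a lower demand for antihypertensive treatment at 12 months postpartum compared with those who receive usual postpartum care".
- **Study outcomes, secondary endpoint 1:** elevated BP "or use of/increase in previous use of antihypertensive drug therapy".

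The Statistical analysis section repeats the and/or wording for the 12-month regression on BP. It adds a GEE logistic model of a 5 mm systolic reduction from baseline, and lists the proportion on antihypertensive therapy among the general two-sample comparisons. The Sample size calculation section gives a single 5 mmHg target for BP and does not say which component it refers to.

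**The concern.** There are two separate faults.

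First, antihypertensive need is primary in the objective and in hypothesis 2 but secondary in the endpoint list. It is also not the same variable throughout. The objective and hypothesis speak of need or demand, the endpoint list has use or an increase in use as one limb of a composite, and the analysis section has a simple proportion on therapy.

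Second, the and/or wording, used in the objective, hypothesis 1, the endpoint and the analysis, leaves open whether systolic BP decides, diastolic BP decides, either suffices or both are required. The article gives no hierarchy, no both-must-win rule and no division of alpha.

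What is at stake is the meaning of a positive trial. If any one of two or three variables can carry the claim, the chance of a false claim rises, and two readers could reach opposite verdicts from the same results.

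**Working it through.** **1. The plan's own figure.** The article randomizes 278 for a 5 mmHg difference after 30% loss. It states no SD, alpha or power for this, so 278 cannot be derived from its stated inputs. With n per arm = 2(1.96 + 0.8416)² × SD² / 5² (two-sided 5%, power 80%):

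- SD 12.4 (back-solved): 2 × 7.849 × 153.76 / 25 = 96.6, so 97 per arm, 194 in total; 194 / 0.7 = 277.1, so 278.
- SD 13 (pilot overall 12-month systolic SD, Table 1): 2 × 7.849 × 169 / 25 = 106.1, so 107 per arm, 214 in total; 214 / 0.7 = 305.7, so 306. Multiplying by 1.3 instead gives 279.

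The figure therefore fits one comparison at an undivided two-sided 5%, but that is an inference.

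**2. Assumptions for the error rates.** Two-sided 5% per route (the article mentions only 95% confidence intervals). Correlations between test statistics are assumed, as the article gives none: 0.5 to 0.8 for systolic with diastolic, and 0.2 to 0.4 for drug use with each BP.

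**3. Two routes (systolic or diastolic).** The two-sided rate is 1 − P(|Z₁| ≤ 1.96 and |Z₂| ≤ 1.96). The benefit-only rate is 1 − P(Z₁ ≤ 1.96 and Z₂ ≤ 1.96), with Z positive for benefit and a nominal 2.5%.

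| Correlation | Two-sided | Benefit only |
|---|---|---|
| 0 (1 − 0.95² = 9.75%) | 9.75% | 4.9% |
| 0.5 | 9.1% | 4.5% |
| 0.7 | 8.3% | 4.2% |
| 0.8 | 7.8% | 3.9% |
| 0.9 | 7.0% | 3.5% |

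**4. Three routes (adding drug use).** The same definitions with a trivariate normal, by simulation with 4 million draws:

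| Systolic-diastolic | Drug use with each BP | Two-sided | Benefit only |
|---|---|---|---|
| 0.5 | 0.2 | 13.4% | 6.8% |
| 0.7 | 0.3 | 12.6% | 6.3% |
| 0.8 | 0.4 | 11.8% | 5.9% |

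Independence would give 1 − 0.95³ = 14.3%.

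**5. Splitting alpha against ordering.** With 97 completers per arm (278 × 0.7 = 194.6), 5 mmHg and SD 13, the standard error is 13 × √(2/97) = 1.867 and the standardized difference is 5 / 1.867 = 2.679.

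- Undivided 5%: Φ(2.679 − 1.960) = 76%.
- Split in two (2.5% each): Φ(2.679 − 2.241) = 67%.
- Split in three (1.67% each): Φ(2.679 − 2.394) = 61%.

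At the back-solved SD of 12.4, holding 80% power would raise the randomized number from 278 to 335 (two routes) or 369 (three). Fixed-sequence testing leaves the first test at 5% and needs no extra participants.

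**The case against.** The strongest reply is that the article is silent on alpha and multiplicity, and that such rules are commonly left to an analysis plan, which is not shown. That stands as far as error control goes. A reader might infer that every route will be tested unadjusted, or that the choice will be made after seeing the data. The article says neither. It does not answer the rest, because the protocol itself states the choice of primary variable, and states it in conflicting ways. An analysis plan would have to override at least one of those statements.

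A second objection is that the third route is weak. The primary endpoint definition leaves drug use out, and the analysis section treats it as one of many two-sample comparisons. This also stands in part: the 12 to 13% applies only if the objective and hypothesis 2 prevail over the endpoint list.

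Third, a reader might take the plan to analyse "we will use different combinations of systolic blood pressure and diastolic blood pressure" as a further way to win. That sentence describes a sensitivity analysis and is not evidence of one. The GEE responder model is closer to the point, since it sits with the analysis of the primary outcome and its standing is not stated.

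Finally, the case for systolic BP is not airtight. The sample size section does not name the component, and hypothesis 1 states its 5 mmHg against those who do not breastfeed, not against the randomized control.

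**Conclusion.** The point holds as a contradiction about what is primary and as a primary endpoint with no deciding variable. Both follow from the text alone.

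The error rates are conditional on two-sided 5% per route and on the assumed correlations: about 8 to 9% two-sided for two routes and 12 to 13% for three. A reader might conclude that a false success could be claimed at well above 5%. The documents do not support that for the and/or wording by itself. Success here means lower BP, and in that direction the two-route rate is about 4 to 4.5%, which is 1.6 to 1.8 times the nominal 2.5% but still below 5%. Only with drug use as a third route does it reach about 6 to 7%.

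The matter should be settled before the analysis, because at present the article does not determine what would count as a positive trial.

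**What to change.** Name one primary variable before outcomes are compared by group. Systolic BP at 12 months is the natural choice: hypothesis 1 pairs the 5 mmHg with systolic, and the responder threshold in the analysis section is 5 mm in systolic BP. Then:

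- test 12-month diastolic BP, and after it one defined antihypertensive-use variable, in fixed sequence, each at 5% only if the one before succeeds;
- state which drug-use definition applies: use alone, or the composite with elevated BP;
- label the GEE responder model as supportive;
- remove and/or from the primary objective, hypothesis 1, the endpoint and the primary analysis, and align those sections. Hypothesis 1 should also state its comparator consistently with the randomized comparison.

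A both-must-win rule or a split alpha would also control the error. The split costs power, as shown above.

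The cost is a protocol amendment with research ethics board approval and a registry update while recruitment is under way. An effect confined to diastolic BP or to drug use could no longer be declared a positive primary result. No additional participants are needed for the change itself.

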**Fig. 2 Fig2:**
[figure not shown]
Elevated Blood Pressure or Use of Anti Hypertensive Medication in Post Partum Women with HDP. This figure shows mean participant blood pressures according to study allocation group (breast feeding self-efficacy based intervention or usual postpartum care) at each of the study time points from the feasibility study “Breastfeeding and Blood pressure patterns in MOthers with hypertensive coMplications of pregnancy (BP-MOM)”. Elevated blood pressure was defined as average automated office blood pressure > 140/90 mmHg or average home blood pressure > 135/85 mmHg

In addition, mean breastfeeding self-efficacy scores (out of a total of 70) were higher in the intervention compared to the control group at 6 weeks (54.7 +/− 9.5 vs. 46.1 *+/−* 13.1), 3 months (55.3 +/− 13.9 vs. 46.3 +/− 15.9) and 6 months (57.2+/− 12.9 vs. 50.3 +/− 18.3). Compared with participants in the usual care group, those who received the BSEI were more likely to be breastfeeding exclusively at 6 weeks (71.4% vs. 44.4%) and 3 months (72% vs. 37%), and to continue breastfeeding to at least 6 months (90% vs. 58%).

The vast majority of participants assigned to the intervention group reported good or very good overall satisfaction with the BSEI at both 3 months (95%, *N* = 19) and 6 months (94%, *N* = 17). Given the positive outcomes and high acceptability of the BSEI, a recruitment rate of 50% within a high-risk obstetrical population, and participant retention of 82% at 6 months, our research team’s steering committee agreed that proceeding with a larger trial was warranted with a protocol adapted for COVID-19 pandemic contingencies (e.g., incorporating options for remote recruitment and measurements).

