**Clinical measures**					
Vital signs (heart rate, respiratory rate, temperature)	**X**				
Blood pressure (SunTech CT40 BP Machine)	**X**			**X**	**X**
Blood pressure (A & D Medical Self-Monitoring BP Machine UA-651)	**X**	**X**	**X**	**X**	**X**
Height, weight	**X**			**X**	**X**
Hip and waist circumference				**X**	**X**

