Blood and urine samples are collected for a routine metabolic panel at 6 months and 12 months, as part of usual postpartum care of those with HDP. A comprehensive metabolic panel is conducted in accordance with local laboratory protocols, and analyzes the following: glycosylated hemoglobin, fasting glucose, lipid profile [includes total cholesterol, non-HDL cholesterol, triglycerides, calculated LDL cholesterol], urine analysis, urine microalbumin to creatinine quantification, serum creatinine, serum electrolytes [sodium, potassium, chloride, bicarbonate, calcium], apolipoprotein-B. At baseline and at 12 months postpartum, we also collect an additional four ml of blood to process for analysis of HDP biomarkers (angiogenic factors, inflammatory factors, circulating plasma micro-RNA). Samples for biomarker analysis (serum and plasma) are kept frozen (− 80 °C) at a local freezer until the end of the recruitment period and will then be shipped on dry ice in batches directly to the laboratory for analysis (see Additional file 6: Appendix 3).

If participants are not able to attend the follow-up clinic visits in person, clinical data can be collected remotely. The study physician will schedule a meeting with the participant via ZOOM™ to conduct the post-HDP follow-up assessment. All participants are provided with a measuring tape upon enrollment for self-measurement of waist and hip circumference, and participants can self-report their weight using their own scales. BP measurements will be obtained remotely using the participants’ home BP monitoring machine loaned to them at recruitment. The participants will also be emailed a requisition for biospecimen collection (blood, urine) that can be conducted at their local walk-in health centers.

Finally, participants who consent will also participate in pragmatic long-term follow-up via data linkage to ascertain cardiovascular outcomes (Fig. 3).

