### Sample size calculation

In order to detect a 5 mmHg between-group differences in postpartum blood pressure and in breastfeeding rates, we are aiming to recruit an approximate of 323 participants (after accounting for a 30% loss to follow-up). Around 278 of these participants (86%) will be randomized to either the breastfeeding intervention group or breastfeeding control group, and 45 participants (14%) who will not be breastfeeding will serve as a comparison group in the observational arm of the study. Accounting for annual delivery rates at each of the study sites and assuming that ~ 8% of deliveries are affected by HDP at all sites, and 70% of those will initiate breastfeeding (an average of general Canadian population initiation rate of ~ 90%, German HDP population rate of 40%, and United States rate of 82% in those with HDP) [48, 94] we anticipated reaching our recruitment target over a two-year period, without accounting for additional recruitment delays due to the pandemic.

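### The 12-month primary endpoint is office BP, but home averages can stand in for non-attenders with no rule on which device counts or how the two are reconciled

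*Protocol article*

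**What the plan says.** **Device.** Study outcomes sets the primary endpoint as systolic and/or diastolic BP from automated office devices, with 12 months as the primary time point. The next sentence reads: "In the case of home blood pressure, an average of four daily measurements over a one-week period is used", with the first day discarded. Data collection says that when a woman cannot come to the clinic, her BP is taken on the "home BP monitoring machine loaned to them at recruitment". Table 2 ticks the office device at baseline, 6 and 12 months. It ticks the home device ("Blood pressure (A & D Medical Self-Monitoring BP Machine UA-651") at all five time points. Footnote b to Table 1 reports that the pilot's 12-month BP combined home and office values under pandemic restrictions.

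**Cut-offs.** The Fig. 2 legend defines elevated BP in the pilot as "average automated office blood pressure > 140/90 mmHg or average home blood pressure > 135/85 mmHg". For this trial, Study outcomes puts the automated-device cut-off at 135/85.

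**Analysis.** Statistical analysis plans an intention-to-treat comparison, a generalized linear model on the continuous readings adjusted for observed imbalances, and a logistic GEE on a 5 mmHg systolic fall since baseline. No device term appears.

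**Drugs.** The second primary hypothesis is that the intervention group "will have a lower demand for antihypertensive treatment at 12 months postpartum compared with those who receive usual postpartum care". Drug use enters a secondary composite and is compared as a proportion.

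**The concern.** An office value is the mean of five readings at one sitting, taken by trained staff. A home value is a self-taken mean of about 24 readings (4 a day over the 6 days kept). If the two differ on average, a 12-month variable holding some of each carries a device effect. In an open-label trial in which only one arm receives proactive calls, clinic attendance could differ by arm, and the device effect would then enter the treatment contrast in either direction. The responder and change analyses have a second exposure: an office baseline set against a home value at 12 months mixes a device change with a BP change.

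Antihypertensive use raises a smaller point. If usual care has more treated women, as the protocol predicts, drugs pull usual-care readings down and the observed difference shrinks.

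**Working it through.** **1. The plan's own figure.** The target is stated as: "In order to detect a 5 mmHg between-group differences in postpartum blood pressure and in breastfeeding rates". The numbers are "Around 278 of these participants (86%) will be randomized" and "after accounting for a 30% loss to follow-up". Alpha, power and SD are not given. Assuming two-sided 5% and 80% power:
- n per arm = 2 × (1.96 + 0.84)² × SD² / 5². SD 12.4 gives 97 per arm, and 194 / 0.70 = 278 after rounding up.
- The pilot's overall 12-month SD of 13 gives 107 per arm and 214 / 0.70 = 306.

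So 278 is reproduced only under an assumed SD. Evaluable women: 278 × 0.70 = 194.6, about 97 per arm.

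**2. Office-home offset.** The pilot cut-offs give 140 − 135 = 5 mmHg. This trial's automated cut-off of 135 against the pilot's home cut-off of 135 gives 0. The range is therefore 0 to 5 mmHg. Cut-offs are only a proxy for a mean offset, since the pilot's 12-month systolic mean was 118.

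**3. Shift from device mixing** = offset × arm difference in home share. The arm differences are assumptions.

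| Offset (mmHg) | 0 points | 10 points | 20 points | 30 points |
|---|---|---|---|---|
| 0 | 0 | 0 | 0 | 0 |
| 2.5 | 0 | 0.25 | 0.5 | 0.75 |
| 5 | 0 | 0.5 | 1.0 | 1.5 |

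The largest entry is 1.5 / 5 = 30% of the target.

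**4. Chance imbalance alone.** With a home share of 0.8 (27 of 34 pilot women were remote at 12 months) and 97 per arm, SE = √(2 × 0.8 × 0.2 / 97) = 0.057. The 95% range is ±11 points, or ±0.56 mmHg at a 5 mmHg offset.

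**5. Equal home use.** There is no shift. The SD rises from 13 to √(13² + 5² × 0.8 × 0.2) = 13.15, and power for 5 mmHg at 97 per arm moves from 0.76 to 0.75.

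**6. Responder definition.** With a 5 mmHg offset, a woman whose BP has not changed but who moves from office to home shows an apparent fall of 5 mmHg, which is the whole threshold. This can alter who is classed as a responder even when the arms are balanced; it favours an arm only if home use differs.

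**7. Antihypertensives.** Shift = drug effect × arm difference in treated share. The documents give neither number. Assuming 5-10 mmHg and 10-20 points: 5 × 0.10 = 0.5 up to 10 × 0.20 = 2.0 mmHg, toward zero if usual care is treated more.

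**8. What a 1 mmHg loss costs.** If the observable effect is 4 rather than 5 mmHg, power at 97 per arm falls from 0.80 to 0.61 (SD 12.4) or from 0.76 to 0.57 (SD 13).

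**The case against.** **Pooling is not stated outright.** The home-averaging sentence is needed in any case, because only the home device is scheduled at 6 weeks and 3 months. The remote-visit text describes data collection, not analysis. This stands in part: substitution is a reading of several passages together. But the sentence sits in the primary-endpoint paragraph, the pilot combined the sources at this time point, and nothing bars it here. Which measurement is the primary value belongs to the endpoint definition, not to detail that can be left for later.

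**The sizes are assumed.** This stands. No home share by arm is given. Both arms have the same usual-care clinic visits at 6 and 12 months, and lactation support ends by 6 months. The pilot's remote share is an overall figure under restrictions and says nothing about a difference between arms.

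**Drug handling is no defect.** This largely stands. Comparing observed BP by intention to treat is a legitimate treatment-policy contrast, drug use is analysed separately, and an analysis plan not shown may say more. A reader might infer that the two primary hypotheses defeat each other, but the first is worded against women who do not breastfeed and only the second against usual care.

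**Home BP as the primary device.** A reader might infer from Table 2 that a seven-day home average exists at both baseline and 12 months. It does not establish that: baseline is the delivery hospitalization, when the monitor is first loaned, and the week of readings is described only before follow-ups.

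**Conclusion.** The endpoint is badly fixed on one point: the 12-month primary value is office BP by definition, but the text lets a home average replace it, with no precedence rule and no device adjustment. The resulting shift in the arm contrast is 0 if home use is equal or the offset is nil, and 0.5-1.5 mmHg (10-30% of the target) if the offset is 5 mmHg and home use differs by an assumed 10-30 points. The 5 mmHg responder analysis is exposed as well when the device changes between visits.

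A reader might infer that the primary result is bound to be distorted by a large part of 5 mmHg. The documents do not support that, because offset, attendance by arm, treated share and drug effect are all unknown. Nor do they support replacing the primary model on account of drug use. The possible dilution of 0.5-2.0 mmHg rests on assumed inputs, runs toward zero if usual care is treated more, and so would not create a false benefit. It justifies a sensitivity analysis only.

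**What to change.** 1. State that the primary 12-month value is the office reading and that a home average is never substituted for it.
2. Impute missing office BP with the 12-month home average as an auxiliary variable. Both devices are scheduled for everyone at 12 months, so attenders with paired readings supply the office-home relation.
3. For change-from-baseline and responder analyses, use the same device at baseline and 12 months.
4. Report the 12-month home average in all women as a sensitivity analysis.
5. Keep intention-to-treat on observed BP as primary. Pre-specify one sensitivity analysis in which readings on antihypertensives are right-censored at the recorded value (censored normal regression). Its normality and censoring assumptions cannot be verified, which is why it should not be primary.

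**Cost:** wording, some imputation work and a slightly wider confidence interval. No new data are needed, since both BP measures and medications are already collected. If in-person attendance were as low as in the pilot (7 of 34), only about 195 × 7/34 = 40 women could have paired readings and the interval would widen more, so attendance by arm should be tracked and reported.
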